## Abstract

**Background:**

Many adolescents in residential care have been exposed to prolonged traumatic experiences such as violence, neglect, or abuse. Consequently, they suffer from posttraumatic stress. This not only negatively affects psychological and behavioral outcomes (eg, increased anxiety, depression, and aggression) but also has adverse effects on physiological outcomes, in particular on their neurobiological stress systems. Although current evidence-based treatment options are effective, they have their limitations. An alternative to traditional trauma treatment is meditation-based treatment that focuses on stress regulation and relaxation. Muse is a game-based meditation intervention that makes use of adolescents’ intrinsic motivation. The neurofeedback element reinforces relaxation abilities.

**Objective:**

This paper describes the protocol for a randomized controlled trial in which the goal is to examine the effectiveness of Muse (InteraXon Inc) in reducing posttraumatic stress and normalizing neurobiological stress systems in a sample of traumatized adolescents in residential care.

**Methods:**

This will be a multicenter, multi-informant, and multimethod randomized controlled trial. Participants will be adolescents (N=80), aged 10 to 18 years, with clinical levels of posttraumatic symptoms, who are randomized to receive either the Muse therapy sessions and treatment as usual (intervention) or treatment as usual alone (control). Data will be collected at 3 measurement instances: pretest (T1), posttest (T2), and at 2-month follow-up. Primary outcomes will be posttraumatic symptoms (self-report and mentor report) and stress (self-report) at posttest. Secondary outcomes will be neurobiological stress parameters under both resting and acute stress conditions, and anxiety, depression, and aggression at posttest. Secondary outcomes also include all measures at 2-month follow-up: posttraumatic symptoms, stress, anxiety, depression aggression, and neurobiological resting parameters.

**Results:**

The medical-ethical committee Arnhem-Nijmegen (NL58674.091.16) approved the trial on November 15, 2017. The study was registered on December 2, 2017. Participant enrollment started in January 2018, and the results of the study are expected to be published in spring or summer 2021.

**Conclusions:**

Study results will demonstrate whether game-based meditation therapy improves posttraumatic stress and neurobiological stress systems, and whether it is more effective than treatment as usual alone for traumatized adolescents.

**Trial Registration:**

Netherlands Trial Register NL6689 (NTR6859); https://www.trialregister.nl/trial/6689

**International Registered Report Identifier (IRRID):**

DERR1-10.2196/19881

## Introduction

### Background

Rates of chronic traumatic exposure among adolescents in residential care are staggering. Over 90% of these adolescents have been exposed to domestic violence, neglect, or emotional, physical, or sexual abuse at a young age [1]. Most of these traumatic experiences take place in the primary caregiving environment, even though caregiver support is essential for adolescents’ attachment, resilience, and stress adaptation [2]. Abuse by caregivers is probably the most interfering stressor that they can experience. Early traumatization interferes with adolescents’ healthy development [3]. It can have devastating effects on their psychosocial development [2], physical health [4], and neurobiological stress response systems [3,5-7].

### Neurobiological Stress Systems

Stress activates the autonomic nervous system and the hypothalamic-pituitary-adrenal axis to produce an appropriate stress response. The autonomic nervous system consists of the sympathetic nervous system and the parasympathetic nervous system. Activation of the sympathetic nervous system occurs rapidly after stress exposure—usually within milliseconds to seconds. When confronted with a stressor, the sympathetic nervous system activates physiological processes frequently referred to as the *fight or flight* response [8]. The increase in sympathetic nervous system activity is reflected by a shorter pre-ejection period (the length of time between the contraction of the heart and the ejection of blood out of the heart into the aorta), corresponding with a higher heart rate [9]. When the stressor disappears, the parasympathetic nervous system inhibits sympathetic activation and facilitates bodily homeostasis (ie, recovery and digestion) [8]. Generally, it has been assumed that the sympathetic nervous system and parasympathetic nervous system are reciprocally coupled: when sympathetic nervous system activity increases, parasympathetic nervous system activity decreases, and vice versa. However, various individual variations of autonomic nervous system and parasympathetic nervous system contributions to stress responses exist [10,11]. One key parameter of the parasympathetic nervous system is respiratory sinus arrhythmia, also referred to as vagal tone. Respiratory sinus arrhythmia is a measure of heart rate variability that represents parasympathetic nervous system control over heart rate and occurs at the frequency of respiration and that facilitates adaptive responses to the environment [12,13]. Lower respiratory sinus arrhythmia is associated with more internalizing and externalizing problems [14] and may increase the risk on internalizing problems after trauma [15,16].

The response of the hypothalamic-pituitary-adrenal axis is slower and has a longer duration than that of the sympathetic nervous system [8,17]. The primary effectors of the hypothalamic-pituitary-adrenal axis system are glucocorticoids (steroid hormones). These have a slower onset and longer duration than the catecholamines of the sympathetic nervous system. Stress activates the paraventricular nucleus of the hypothalamus, which releases corticotropin-releasing hormone within a few minutes, usually peaking 15 minutes after the stressor [18]. This stimulates the production of adrenocorticotropic hormone by the pituitary, which in turn signals the adrenal gland to release cortisol. Cortisol is also produced during nonstressful situations, referred to as basal cortisol [17]. Research in adolescents on the impact of trauma on cortisol shows evidence for a link between trauma and hypothalamic-pituitary-adrenal axis alterations but is characterized by the lack of a clear physiological profile. Exposure to trauma has been related to increased [19,20] and decreased cortisol levels [19-21].

In healthy individuals, the autonomic nervous system and the hypothalamic-pituitary-adrenal axis together generate adaptive responses in the face of acute threat. However, the experience of multiple, prolonged traumatic events can result in chronic activation of these stress systems, even when the original stressor has disappeared [2]. The unpredictable and ongoing nature of the traumatic events make these adolescents feel as if they are under constant threat of survival [22]. Unsurprisingly, the adverse effects of trauma become more severe and pervasive as the trauma lasts for a long period or the number of traumatic events increases [1,23].

### Trauma Treatment

Although trauma-focused cognitive behavioral therapy and eye movement desensitization and reprocessing are well-established effective treatments for traumatized adolescents [24], there are some inherent limitations. Both treatment models incorporate exposure techniques, verbal expression, and rely on the integration of cognition, emotion, and physiology. In order for the therapy to succeed in promoting change, sufficient capacity to regulate these systems is required [25]. Yet, traumatized adolescents often lack the capacity to control and regulate their impulses and emotions [2,26], and even when adolescents do exhibit the necessary skills in order for therapy to succeed in promoting change, residential care provides an often chaotic living environment that impedes the development of a therapeutic relationship and treatment progress [27]. Also, adolescents are often not motivated to talk about their experiences and re-experience their traumatic past [28].

Given the difficulties faced in traditional trauma treatment, alternative forms of intervention have gained popularity. The focus has shifted from mainly cognitive-oriented and verbally dependent therapies to interventions that target physiological sensations. One promising approach is fostered by meditation interventions that focus on adolescents’ stress regulation abilities. Meditation techniques (eg, deep-breathing practices) focus on one’s own bodily sensations and increase a sense of control over the body. Not only can feelings of stress be reduced and emotion-regulation capacities improved, individuals also showed beneficial changes in cardiovascular activity [29-31]. Meditation can restore activity and connectivity in brain regions associated with posttraumatic symptoms [32], lead to more balanced patterns of neurobiological stress responses [33], and modulate both hypothalamic-pituitary-adrenal axis and autonomic nervous system reactivity [34]. Research on the effectiveness of meditation interventions for posttraumatic stress shows encouraging findings. Most studies have been conducted among adults [32-36], but promising outcomes have been reported in traumatized adolescents too [37].

### Game-Based Therapy

This study aims to test the efficacy of game-based neurofeedback meditation therapy as an addition to treatment as usual in a population of traumatized adolescents in residential care. Gaming forms a novel strategy to engage adolescents into treatment and holds several advantages over traditional therapy. Videogame or gamified interventions make use of adolescents’ intrinsic motivation [38], while conventional treatment often depends upon imparting psychoeducational information, a didactic style of learning that contains few elements that are intrinsically motivating. Yet, motivation is an important predictor of treatment effectiveness [39], and adolescents in residential institutions are usually characterized by a lack of motivation to change their behavior [40]. Gamified treatment teaches adolescents techniques and skills but with less thinking and more doing [38]. This way of learning suits them better than memorizing certain principles [41]—conventional therapy—does [42]. Game-play is characterized by its repetitive nature. Repetition promotes long-term learning [43], and thus may foster generalization of its effects to adolescents’ daily lives. There have been some studies [44-46] conducted among adolescents in residential institutions that evaluated biofeedback videogame interventions. Results showed high user satisfaction, minimal attrition, and improved emotion-regulation [44-46].

Recently, the authors conducted a feasibility study [47] that evaluated 3 game-based meditation interventions in traumatized adolescents in residential care. The interventions incorporated either bio- or neurofeedback and were assessed on their potential to improve physiological stress regulation, user satisfaction, and preliminary effectiveness on posttraumatic symptoms, stress, depression, and aggression. The intervention that was evaluated positive on all outcomes and considered the best fit was Muse (InteraXon Inc)—a game-based neurofeedback meditation intervention.

### Objectives

The primary aim of this study is to investigate the effectiveness of Muse as an addition to treatment as usual in reducing posttraumatic symptoms (self- and mentor report) and stress (self-report) compared with treatment as usual in traumatized adolescents in residential care. We expect that playing Muse will result in a greater reduction of posttraumatic symptoms and stress than treatment as usual alone.

As a secondary aim, we will investigate the effectiveness of Muse on neurobiological stress systems under both resting and social stress conditions. It is hypothesized that participants who play Muse will show normalized neurobiological parameter compared to participants in the control group. We will also assess the effects of playing Muse on anxiety (self-report), depression (self-report) and aggression (self- and mentor report). It was expected that playing Muse would result in reduced anxiety, depression, and aggression.

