### Statistical Analysis

To assess intervention efficacy, we will use repeated measure analysis of variance to detect differences in mean outcome scores between the 2 groups at T2 and at 2-month follow-up. All analyses will be conducted in accordance with the intention-to-treat principle. Missing data will be imputed using Markov Chain Monte Carlo [74]. Results will be expressed as differences in mean scores between the 2 groups with 95% confidence intervals. *P* values<.05 will be considered statistically significant.

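### For cortisol, a comparison of group means does not test the hypothesis that Muse normalises stress physiology, because the protocol links trauma to both raised and lowered levels

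*Protocol article*

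**What the plan says.** Objectives states the secondary hypothesis on stress physiology as "participants who play Muse will show normalized neurobiological parameter compared to participants in the control group". The neighbouring hypotheses there have a direction: less posttraumatic stress, anxiety, depression and aggression. This one has none.

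Neurobiological Stress Systems describes the research on trauma and cortisol in adolescents as "characterized by the lack of a clear physiological profile" and continues: "Exposure to trauma has been related to increased [19,20] and decreased cortisol levels [19-21". For one autonomic parameter the same section does give a direction: "Lower respiratory sinus arrhythmia is associated with more internalizing and externalizing problems". It also notes that "various individual variations of autonomic nervous system and parasympathetic nervous system contributions to stress responses exist", but does not say that autonomic abnormality runs both ways.

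Statistical Analysis gives one efficacy analysis for all outcomes: "repeated measure analysis of variance to detect differences in mean outcome scores between the 2 groups at T2 and at 2-month follow-up". On reporting: "Results will be expressed as differences in mean scores between the 2 groups with 95% confidence intervals".

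The measurement sections describe how hair cortisol, salivary cortisol and the autonomic parameters are obtained. They name no normal value or comparison group for cortisol, and no direction in which it should move.

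**The concern.** Normalisation is movement towards a reference from whichever side a participant starts. The analysis asks only whether one arm's mean ends up higher or lower than the other's. On the protocol's own account of cortisol, the two questions can come apart in two ways:

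- **Missed effect.** Raised levels fall, lowered levels rise, and the shifts cancel in the mean.
- **False label.** The mean falls significantly, but participants who started low have moved further from normal. With no direction fixed in advance, either sign could be reported as normalisation.

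Normalising the stress systems is part of the goal in the abstract, so this affects what the trial may conclude about cortisol. The primary outcomes are not touched.

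**Working it through.** **1. The plan's own figure.** From Sample Size Calculation: d = 0.30, correlation 0.60, power 0.80, N = 72, raised to 80 for 10% attrition. With f = d/2 = 0.15 and two time points, λ = f²·N·m/(1−ρ) = 0.0225 × 72 × 2 / 0.40 = 8.1. On 1 and 70 degrees of freedom at α = 0.05 the power is 0.801, and 72/0.90 = 80. So N reproduces, and 72/2 = 36 per arm is used below. This calculation sizes a difference in means and is not in dispute.

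**2. Cancellation.** Assume a share p of participants lies D above normal and 1−p lies D below. Controls do not change, and every treated participant moves fully to normal. The expected difference in mean change is

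p(−D) + (1−p)(+D) = −D(2p−1).

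At p = 0.5 it is 0. At p = 0.7 and D = 1 it is −0.4. If only a fraction r of the deviation is removed, multiply by r.

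**3. Rejection rate of the mean comparison.** Simulation with 20,000 replicates and a t test on T2−T1 change, which is equivalent to the two-group, two-time interaction test. D is in SD units of the variation around each participant's set point, and that variation has T1–T2 correlation 0.60. 36 per arm:

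| Share raised, p | D = 1.0 | D = 1.5 |
|---|---|---|
| 0.5 | 5% | 5% |
| 0.6 | 12% | 16% |
| 0.7 | 33% | 48% |
| 0.8 | 66% | 85% |
| 0.9 | 92% | 99% |
| 1.0 | >99% | 100% |

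These rates assume complete normalisation of everyone treated. In the same simulation, absolute distance from a correctly known reference gives about 43–44% (D = 1.0) or 91% (D = 1.5), whatever p is. The documents name no such reference.

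**4. Group-by-T1-level interaction.** True levels are +1 or −1 in equal shares, with independent error of SD e at each wave, so the T1–T2 correlation in controls is 1/(1+e²). Setting e = 0.5 gives 1/1.25 = 0.80. The protocol's 0.60 needs e² = 1/0.60 − 1 = 0.667, so e = 0.816. Power at 36 per arm:

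| Deviation removed | correlation 0.80 | correlation 0.60 | mean comparison |
|---|---|---|---|
| half | 87% | about 39% | 5% |
| 30% | 41% | 13–15% | 5% |

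I re-ran this with 10,000 replicates and obtained 38% and 15% at correlation 0.60. With no effect the interaction rejected 3%, so its power is not bought with false positives.

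**5. Does a flatter slope show normalisation?** Suppose Muse simply halves every participant's level (mean 4, SD 1, error SD 0.5), so that low starters fall further. The T2-on-T1 slope in the Muse arm is then significantly flatter in about 83% of runs. A significant slope interaction is therefore not enough; the sign of the group difference at low and at high T1 levels has to be examined.

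**The case against.** **Direction is not absent everywhere.** True. Lower respiratory sinus arrhythmia is presented as worse, and sympathetic activation is tied to a shorter pre-ejection period and higher heart rate. For such parameters a mean difference is a sensible test. A reader might infer that the whole neurobiological objective can be neither supported nor refuted; the documents do not support that, because the two-way statement concerns cortisol only.

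**The protocol also speaks of chronic activation of the stress systems.** This could imply that raised cortisol is expected. But it is worded as a possible result of prolonged trauma, it follows the statement that cortisol has been found both raised and lowered, and Objectives does not turn it into a direction.

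**The mix in this sample is unknown.** True. Conflicting findings in the literature do not show that these participants split evenly. If 80–90% lay on one side, the mean comparison would recover 66–99% power under the assumptions above. The cancellation is a possibility that the protocol's premise opens, not a prediction.

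**A condensed article may leave the definition to another document.** It may. The point does not rest on the omission, however: the analysis that is stated does not answer the hypothesis that is stated.

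**The alternative is weak.** This also stands. The 87% in the working needs a T1–T2 correlation of 0.80; at the protocol's 0.60 the figure is about 39%.

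**Conclusion.** The mismatch is real for hair and salivary cortisol and for any other parameter left without a direction. Followed as written, the analysis can miss two-sided normalisation, with rejection at about the 5% level for an even mix and reduced power for an uneven one. It also leaves open calling a one-way shift normalisation. The algebra −D(2p−1) is general for equal deviations. The power figures rest on assumed values of p and D, on 36 per arm, and on correlation 0.60, which the protocol states for its power calculation and not for cortisol.

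A reader might go further and infer that the cortisol comparison will show nothing, or that a slope interaction would settle the matter. Neither follows: the mix is unknown, and a uniform proportional fall also flattens the slope. This is a secondary-outcome point about which conclusion the data can carry; the primary outcomes and N = 80 are unaffected.

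**What to change.** In Objectives and Statistical Analysis, choose one of the following for hair and salivary cortisol, before the arms are compared.

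1. **Restate the hypothesis** as a difference in mean cortisol between groups, and do not conclude normalisation from it.
2. **Prespecify a group-by-T1-level analysis** of T2 cortisol. Report the estimated group difference, with its 95% confidence interval, at a low and at a high T1 level named in advance. Claim normalisation only if, relative to control, high levels fall and low levels rise. This reading assumes that normal lies between the two levels, and the text should say so. Use absolute distance from a reference only if the reference value is named beforehand.

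Keep the mean comparison for parameters with a stated direction, such as respiratory sinus arrhythmia, and write that direction into the hypothesis.

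Cost: wording and one added model, with no new measurements. Option 2 has low to modest power (about 39% if half of a 1-SD deviation is removed, 13–15% if 30% is removed, at correlation 0.60 and 36 per arm). It should be labelled a secondary, low-power test, and a non-significant result should not be read as evidence against normalisation.

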## Methods

### Study Design

This study is a multicenter randomized controlled trial with 2 parallel intervention groups. Outcomes will be compared at 3 measurement instances: before the intervention (T1), immediately after the intervention (T2), and at a 2-month follow-up. Participants will be randomly assigned to the intervention or the treatment-as-usual (control) group, stratified by gender and intellect to ensure equal ratios of participants in both groups.

### Study Setting

Recruitment will take place in 3 residential institutions in The Netherlands that provide open and secured care for children and adolescents with and without intellectual disability. Residential care is the most intensive form of youth care and includes out-of-home placement and 24-hour care. These adolescents are unable to live at home due to severe psychiatric or behavioral problems, parental problems, or an unsafe home environment—often a combination of all of these. Adolescents live in group homes with group care workers as substitute care givers and receive treatment to target problem behavior. Residential care is often seen as a last-resort solution when there are no other options for treatment [48].

### Inclusion and Exclusion Criteria

Inclusion criteria are (1) clinical levels of posttraumatic symptoms, measured as a score of 30 or higher on the Children’s Revised Impact of Event Scale (CRIES-13) [49]; (2) age between 10 and 18 years; (3) capable of understanding and speaking Dutch; (4) active informed assent to participate in the study from participants themselves and active consent from legal guardians when participants are under the age of 16 (obtained by the first author). Exclusion criteria are (1) negative clinician advice, for example, when the participant already has other forms of treatment and the clinical fears that treatment burden would become too heavy (at this stage, participants are not randomized yet, so this exclusion criterion will affect both groups equally); (2) simultaneous participation in another clinical intervention study; (3) acute psychotic symptoms; (4) current or recent (within the previous 3 months) trauma treatment, specifically eye movement desensitization and reprocessing or trauma-focused cognitive behavioral therapy specifically targeting posttraumatic symptoms. There are no restrictions for other types of interventions that participants may receive (eg, medication, individual therapy, or group therapy). We will keep track of additional interventions and use them as covariates in the analyses, if necessary.

